### Advantages of a new format of tDCS: HD-tDCS

A main drawback of traditional transcranial direct current stimulation (tDCS) is the spatial crudity of its effect. The highest cortical current density may not occur directly under the target electrode [7], which probably alters the effects of tDCS and contributes to the inconsistent results of existing tDCS studies [8, 9]. HD-tDCS was developed as a solution to tackle this issue with high precision and accuracy. Similar to conventional tDCS, which utilizes an anode and a cathode placed on the scalp to establish a unidirectional current flow, HD-tDCS also involves the use of both anode and cathode electrodes, typically consisting of more than two smaller electrodes. In the latter, precise delivery of current to the intended target site is its primary advantage. Although various montages can be explored, the “4X1 ring” montage is by far the most commonly used. It utilizes a center anode electrode surrounded by four return cathode electrodes and confers HD-tDCS with the ability to achieve a single desired activity without inducing cortical stimulation due to opposite polarity [10, 11]. The density of the cortical field and spatial focality can be modulated by changing the diameter of the ring of electrodes [12]. In addition to enhancing the spatial focality of stimulation, the augmented effects of neuroplasticity may also manifest in longer-lasting after-effects, as demonstrated in a previous study on HD-tDCS [10]. At the same time, the tolerability was found to be comparable to that of conventional tDCS [13]. No HD-tDCS study of MDD with ADS has yet been performed. Therefore, our team conducted a pilot study to test the effects and tolerability of HD-tDCS on MDD patients with ADS [14].

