### Results from our pilot study

A pilot study [14] was conducted by our team in 39 adults who have MDD with ADS received five consecutive daily sessions of 20-min active or sham HD-tDCS interventions weekly for 2 weeks. The results revealed that the HD-tDCS has significant efficacy in the treatment among MDD patients with anxious distress. The rate of adverse events(e.g., itching, tingling and headache) showed no significant differences between the two groups. Additionally, no severe adverse events or mania was reported. Nevertheless, it should be noted that the trial was of short duration, limited to hospitalized patients, and did not include an evaluation of cognitive or daily functioning. A double-blinded randomized controlled trial (RCT) with an adequate sample size and adequate study periods is warranted to confirm the efficacy of HD-tDCS as an augmentation therapy with antidepressants in MDD patients with ADS.

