## Methods

### Recruitment

We will approach patients in the Zhenjiang Mental Health Center outpatient and inpatient units. Our inpatient and outpatient care units follow up at least 5000 patients with MDD each year. We will ensure the completion of the study schedule in accordance with the current protocol. Standard clinical care will continue to be provided to all participants upon completion of the trial at our healthcare facility. Recruitment, pre-participation screening, allocation, intervention, and data collection will be conducted between Jun 2023 and November 2025. Our plan is to conclude the study by the end of 2026 and make the results available for analysis. The current study protocol adheres to the SPIRIT 2013 recommendations (Standard Protocol Items: Recommendations for International Trials) [15]. Figure 1 shows the schedule of enrollment, interventions, and assessments.

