### Eligibility criteria

The inclusion criteria are as follows:Ability and willingness to provide written informed consent for trial participation and undergo all necessary procedures is required;The age range is between 18 and 65 years old;A diagnosis of MDD with ADS according to the Diagnostic and Statistical Manual of Mental Disorders, Fifth Edition (DSM-5), which is assessed by at least one professional psychiatrist; the presence of specifier was evaluated based on DSM-5 criteria, which mandates that MDD patients exhibit at least two out of five symptoms;Han ethnicity;Right-handedness;Adequate auditory and visual acuity to perform requisite inspections;Presence of depressive symptoms ranging from mild to severe, as measured and defined by HDRS-17 scores ≥ 8 and ≤ 52 [16];Willing to remain on maintenance pharmacotherapy for at least 2 weeks before the stimulation initiation and during the total stimulation period.

The exclusion criteria are as follows:The presence of severe systemic illnesses, including but not limited to severe hepatic, renal, endocrine, cardiovascular, respiratory, hematological, or oncological diseases that are deemed by the investigator as unsuitable for participation in the trial;Any laboratory examination that shows clinically significant abnormalities and may have an impact on the health of participants, as determined by the investigator;A history of any significant medical illness, such as neurological disorders (e.g., cerebral trauma, seizure disorder, etc.), that would render the participant unsafe for trial participation in the investigator’s opinion;Known to have current psychosis as determined by the DSM-5 criteria or a history of a non-mood psychotic disorder;Current substance abuse, including alcohol and/or illicit or prescription drugs;Current or planned pregnancy and/or lactation during the trial;A scalp with abnormal conditions, such as open wounds;A score = 4 for item 3 (suicide) on the HDRS-17;Having undergone or currently undergoing modified electroconvulsive therapy (MECT) or repetitive transcranial magnetic stimulation (rTMS) within the past month;Concurrent participation in another clinical trial or participation within 1 month prior to randomization is not allowed.

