### Sham–control HD-tDCS group

The procedure for sham stimulation will be identical, with the exception that the electrical current will gradually decrease to zero after 30 s, thereby producing an equivalent initial sensation of HD-tDCS. The stimulator will be programmed to automatically control the current, eliminating the need for operator intervention. The computer will be positioned posterior to the subjects’ craniums, thereby obstructing their visual access to the readout.

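### The exclusion criteria cover recent MECT and rTMS but omit tDCS and HD-tDCS, the modality under test, so recent, concurrent or pilot exposure is admissible

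*Protocol article*

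**What the plan says.** The Eligibility criteria section of the protocol article sets out the inclusion and exclusion criteria as a list. One exclusion concerns brain stimulation: "Having undergone or currently undergoing modified electroconvulsive therapy (MECT) or repetitive transcranial magnetic stimulation (rTMS) within the past month". One concerns other trials: "Concurrent participation in another clinical trial or participation within 1 month prior to randomization is not allowed". No criterion names tDCS or HD-tDCS, past or current, and none requires patients to be new to stimulation.

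Four other places bear on this:

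- **Pilot.** Results from our pilot study reports a study that "was conducted by our team in 39 adults who have MDD with ADS received five consecutive daily sessions of 20-min active or sham HD-tDCS interventions". By its own account, "the trial was of short duration, limited to hospitalized patients".
- **Recruitment.** "We will approach patients in the Zhenjiang Mental Health Center outpatient and inpatient units".
- **Sham.** In the sham arm, "the electrical current will gradually decrease to zero after 30 s, thereby producing an equivalent initial sensation of HD-tDCS".
- **After-effects.** The Introduction's section on the advantages of HD-tDCS says that "the augmented effects of neuroplasticity may also manifest in longer-lasting after-effects".

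The section on concomitant care leaves usual care as it is in both arms and bars no other tDCS.

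**The concern.** The investigators evidently regard recent neuromodulation as a reason to keep a patient out, since they wrote a one-month rule for two modalities. The rule omits the modality most closely related to the intervention. Read literally, a patient who had rTMS three weeks ago is excluded, and a patient who had tDCS outside a trial yesterday is not.

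Two things are at stake. The first is participant blinding. The sham works by imitating how a session starts, and a patient who has already had full active sessions has something to compare it with. The primary outcome is a rated symptom scale that draws on what the patient reports, so expectation can reach it even when the evaluator is blinded. The second is carry-over. The article itself raises the possibility of lasting after-effects, and a patient still under the influence of an earlier course does not enter on the same footing as one who is not. Blinding is the more direct of the two.

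**Working it through.** The plan gives no figure on this point, so the check is mainly one of reading the criteria against each other.

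**Step 1: which criterion catches which patient?**

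| Prior exposure | Neuromodulation exclusion | Other-trial exclusion | Result as written |
|---|---|---|---|
| MECT or rTMS, past month | applies | – | excluded |
| tDCS or HD-tDCS outside a trial, recent | not named | does not apply | not excluded |
| tDCS or HD-tDCS outside a trial, ongoing | not named | does not apply | not excluded |
| Pilot participation within one month of randomisation | not named | applies | excluded |
| Pilot participation earlier than that | not named | does not apply | not excluded |

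The remaining exclusions (systemic illness, laboratory findings, neurological and other medical history, psychosis, substance abuse, pregnancy, scalp condition, suicide item) do not address earlier stimulation.

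**Step 2: is the exposure foreseeable?** The pilot population had the same diagnosis. Its patients "received five consecutive daily sessions of 20-min active or sham HD-tDCS interventions weekly for 2 weeks", which is the stimulation time and schedule given in the Interventions section of this trial. Entry needs an HDRS-17 score of only 8 or more, so a former pilot patient with residual or returning symptoms could qualify. The article gives neither the pilot's site nor its dates, and it does not say how many of the 39 had active stimulation.

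**Step 3: how many could there be?** The documents do not say. A rough illustration from their own figures assumes that the pilot was run at this site, that all 39 are still followed there, and that they enter in proportion to their share of the pool.

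- Pool of 5000 MDD patients a year (Recruitment): 39 / 5000 × 58 = 0.45 pilot patients in the whole trial.
- Pool restricted to those with ADS, at the 50–65% given in the Introduction, that is 2500 to 3250 patients: 39 / 2500 × 58 = 0.90, and 39 / 3250 × 58 = 0.70.

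Some of these would have had sham. Preferential re-approach of known patients would raise the figure, and non-trial tDCS would add to it; the documents quantify neither. Each exposed patient is 1/29 = 3.4% of an arm.

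**Step 4: which way would a bias run?** It cannot be fixed. The outcome is change from baseline. A benefit from an earlier course that persists is already in the baseline score. One that fades after baseline would worsen a sham patient's change and widen the contrast. An earlier non-responder in the active arm would narrow it. Randomisation balances prior exposure on average, though not reliably with 29 per arm.

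**The case against.** The case on the other side is substantial.

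- **The number may be very small.** The section on post-trial care describes standard care as behavioural, psychosocial and drug treatment, without tDCS. The Ethics and dissemination section presents the approach as one for the near future. This stands: recent clinical tDCS is a case the criteria allow, not one the documents show to be common.
- **The pilot route is an inference.** It rests on the pilot having been run by the same team. This stands. A reader might infer that 39 treated patients are waiting in the recruitment pool, but the 39 had active or sham, and the pilot's site and dates are not given.
- **The blind is not shown to fail.** Evaluators are blinded, a blinding assessment is scheduled at T3, and itching, tingling and similar events did not differ significantly between the pilot's arms. A reader might infer that experienced patients will recognise the sham; no document demonstrates that. Equally, a null comparison in 39 patients does not exclude it, and an assessment at the last visit can detect unblinding but not prevent it.
- **Dilution has no basis in the text.** A reader might assume that 10% or 20% of active patients are former non-responders and shrink the planned g of 0.743 to 0.743 × 0.90 = 0.67 or 0.743 × 0.80 = 0.59. That needs about 3 to 6 of 29 active patients (29 × 0.10 = 2.9; 29 × 0.20 = 5.8), and nothing supports such shares.
- **The objective is not limited to first courses.** The article aims at superiority over sham in MDD with ADS and calls the trial pragmatic. Admitting some previously stimulated patients contradicts no stated aim.

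None of this closes the gap in the criteria. It limits what may be said about the consequences.

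**Conclusion.** The gap is real and follows from the text alone: the eligibility list restricts two forms of brain stimulation and leaves out the one under test, and the one-month trial rule covers only part of what is left. The possible consequences are weaker participant blinding and carry-over. Their size and direction cannot be calculated, because the number exposed, the pilot's site and dates, the split of its 39 patients between active and sham, and the duration of any after-effect are all absent. The illustration of roughly half to one pilot patient in the whole trial rests on strong assumptions and suggests that the number may be small. The documents do not support a claim that the blind will break, that the contrast will shrink by a stated amount, or that the trial no longer answers its question. This is an inexpensive improvement worth making, not a demonstrated bias.

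**What to change.** 1. Add tDCS and HD-tDCS to the existing neuromodulation exclusion, past and ongoing, and name participation in the pilot study explicitly. The length of any look-back period is for the investigators to set and state.
2. Record prior brain stimulation at baseline: modality, date, and active or sham where known. The psychiatric history items named under Demographic data are age at onset, relapses and medication. Treatment history is already taken by direct inquiry and checked against the electronic record, so this is one more item.
3. If exposed patients have already been randomised, keep them in the intention-to-treat analysis and report a sensitivity analysis of the primary outcome without them.

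The change to eligibility needs approval by the ethics committee and an update of the registry record, as the article's section on amendments provides. The downside is a few candidates lost at screening, at a centre that reports following at least 5000 MDD patients a year for a trial of 58.

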### Randomization, concealment, and blinding

The eligibility participants will be randomly assigned to either active or sham HD-tDCS group with a 1:1 allocation. This study will use the Statistical Analysis Software (version 9.3, SAS Institute Inc., Cary, NC, USA) to generate the random allocation sequence. The randomization list will be enclosed in computer-generated opaque envelopes, each labeled with a sequence number on the outside. After the eligible patients have been screened, the researchers will proceed to open the envelopes. The unblinded researchers will create the randomization sequence and allocate participants to treatments. The trained operators responsible for administering HD-tDCS will not be blinded to allocation and, as a result, will be excluded from assessments and data processing. The participants, statisticians, and evaluators will be kept blinded to the treatment allocation. The unblinding process should only be initiated in the event of an emergency, such as the occurrence of any serious adverse events.

### Sample size calculation

The sample size will be determined using G*Power 3.1, based on the findings of a a tDCS meta-analysis of adult patients with MDD [17]. In this study, active tDCS was found to be significantly more effective than sham tDCS for the reduction of depression severity (Hedges’ *g* = 0.743). For a power of 80% and an alpha level of 5%, a total sample size of 48 patients (24 in each group) is required to detect significant differences between the groups. To account for a 20% drop-out rate, a total of 58 patients (29 in each arm) will be recruited.

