**Methods:**

MDD patients with ADS will be recruited and randomly assigned to the active HD-tDCS or sham HD-tDCS group. In both groups, patients will receive the active or sham intervention in addition to their pre-existing antidepressant therapy, for 2 weeks with 5 sessions per week, each lasting 30 min. The primary outcome measures will be the change of depressive symptoms, clinical response, and the remission rate as measured with the 17-item Hamilton Depression Rating Scale (HDRS-17) before and after the intervention and at the 2nd and 6th week after the completed intervention. Secondary outcome measures include anxiety symptoms, cognitive symptoms, disability assessment, and adverse effects.

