### Primary outcome

The primary outcome will be the change of depressive symptoms. The clinical response rate and remission rate, as assessed by the HDRS-17 (17-item Hamilton Depression Rating Scale) at 6 weeks post-intervention were measured. The Chinese version of HDRS-17 has been validated for its psychometric properties and is commonly used to evaluate depressive severity in Chinese patients with depression symptoms [18]. The clinical response is defined as a ≥ 50% reduction from the baseline [19], and a score of 7 or less will be used as an indicator of remission [20].

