### Statistical analysis

Continuous variables will be summarized using the mean and standard deviation measures. Categorical variables will be presented in terms of frequency and percentage. Between-group comparisons will be assessed using the Mann–Whitney *U* test for continuous variables and either the chi-square test or Fisher exact test for categorical variables. The primary outcome will be analyzed based on the intention-to-treat principle, with worst case imputation applied. For repeated continuous outcomes, a mixed linear model will be employed, which includes the interaction between group (active versus sham) and time (baseline, post-assessment, 2-week and 6-week follow-up assessment.

The hypotheses will be tested using unpaired, two-tailed tests at a significance level of 0.05. The software SAS, v.9.4 (SAS Institute Inc.), was utilized.

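### The 80% power rests on a one-tailed comparison of mean depression scores; if response and remission are also primary, as the abstract and discussion say, it does not cover them

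*Protocol article*

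**What the plan says.** The section Sample size calculation takes its effect from a meta-analysis in which "active tDCS was found to be significantly more effective than sham tDCS for the reduction of depression severity (Hedges’ *g* = 0.743"). At 80% power and 5% alpha it concludes that "a total sample size of 48 patients (24 in each group) is required to detect significant differences between the groups", and adds: "To account for a 20% drop-out rate, a total of 58 patients (29 in each arm) will be recruited". It does not say whether the calculation is one- or two-tailed, and it gives no response or remission rate.

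The abstract's Methods paragraph is plural: "The primary outcome measures will be the change of depressive symptoms, clinical response, and the remission rate". The Discussion likewise describes the depressive-symptom outcome at three levels: change, response and remission. The section Primary outcome starts differently. Its first sentence names one primary outcome, the change of depressive symptoms. Response and remission follow under the same heading, with their cut-offs: "The clinical response is defined as a ≥ 50% reduction from the baseline [19], and a score of 7 or less will be used" for remission.

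Under Statistical analysis, group comparisons use "either the chi-square test or Fisher exact test for categorical variables", and "The hypotheses will be tested using unpaired, two-tailed tests at a significance level of 0.05". The primary outcome is analysed by intention to treat with worst-case imputation.

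**The concern.** A mean difference of 0.743 SD on a continuous score does not give the same power once the score is cut at a threshold, because dichotomising discards information. Two of the three measures that the abstract calls primary are such cuts of the HDRS-17. Nothing in the protocol shows what 24 or 29 patients per arm can detect on them, yet the sample-size conclusion speaks of differences between the groups in general.

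The risk lies in interpretation. If the assumed effect is real, a significant mean change beside a non-significant response or remission rate is a likely result. A reader who takes 80% power to apply to all three could see that as a contradiction, or as evidence of no effect on the clinically interpretable outcomes, when low power would explain it.

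**Working it through.** **Inputs from the protocol:** d = 0.743; alpha 0.05; 1:1 allocation; 24 per arm evaluable and 29 per arm recruited; 20% drop-out; two-tailed tests; chi-square or Fisher for categorical variables; worst-case imputation.

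**Inputs assumed:** sham event rates of 10% to 40%; a normal latent score shifted by 0.743 SD; worst-case imputation read as counting each drop-out as a non-event in either arm.

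**1. Reproducing the stated figure.** For a two-sample t-test the non-centrality is d·√(n/2).
- n = 24: 0.743 × √12 = 2.574 on 46 df. One-tailed (critical t 1.679), power is 81.3%. With 23 per arm it is 79.8%, so 24 is the smallest n that reaches 80%, and 48 in total is reproduced.
- n = 24, two-tailed (critical t 2.013): 71.2%.
- n = 29, two-tailed: 0.743 × √14.5 = 2.829 on 56 df (critical t 2.003), 79.4%. Two-tailed 80% needs 30 per arm (80.8%).

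**2. The same effect after dichotomising.** Active rate = Φ(Φ⁻¹(sham rate) + 0.743). For example, with a sham rate of 10%, Φ(−1.282 + 0.743) = Φ(−0.539) = 29.5%. Power comes from full enumeration of two binomials, two-tailed at 0.05. The chi-square test is without continuity correction: z = (difference in proportions)/√(2·p̄(1 − p̄)/n). For drop-outs counted as non-events, both rates are multiplied by 0.8.

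| Sham | Active | 24 per arm, chi-square / Fisher | 29 per arm, all observed | 29 per arm, 20% non-events |
|---|---|---|---|---|
| 10% | 29.5% | 41.7% / 30.1% | 46.7% / 33.6% | 38.1% / 22.7% |
| 20% | 46.1% | 49.9% / 38.4% | 55.8% / 45.5% | 43.6% / 33.1% |
| 30% | 58.7% | 55.2% / 43.2% | 59.5% / 48.8% | 43.5% / 33.7% |
| 40% | 68.8% | 55.5% / 43.5% | 59.8% / 49.1% | 41.8% / 31.7% |

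Between these grid points the maxima are slightly higher: 56.0% (24 per arm) and 60.3% (29 per arm) at a sham rate of 35%, and 44.1% (with non-events) at 25%.

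**3. Separating the number of tails from dichotomising**, at 24 per arm:
- Two-tailed: 71% for means against 30% to 56% for proportions.
- One-tailed: 81% for means against 54% to 67% (chi-square) or 41% to 56% (Fisher) for proportions.

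**4. Sensitivity (two-tailed).**
- A logistic conversion, with log odds ratio 0.743 × π/√3 = 1.348, gives at most about 65% at 24 per arm and 70% at 29 at the tabulated sham rates (65.8% and 70.6% at a sham rate of 35%).
- With the normal shift at 24 per arm, a 5% sham rate gives 19% (Fisher) to 31% (chi-square), and a 50% sham rate gives 40% to 52%.

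No two-tailed scenario reaches 80%.

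**5. Detectable difference at 80% power, two-tailed**, with the active rate rounded up to a whole per cent:
- 24 per arm: from 10% versus 44% (34 points, chi-square) to 30% versus 73% (43 points, Fisher).
- 29 per arm, no losses: from 10% versus 41% (31 points, chi-square) to 30% versus 70% (40 points, Fisher).

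**The case against.** The strongest reply is that the trial has one primary outcome, and it is continuous. The Primary outcome section opens in the singular, Statistical analysis also speaks of a single primary outcome, and the effect size in the sample-size paragraph is expressly one for depression severity. Sizing a trial on its continuous primary outcome alone is normal practice. On that reading the power figures for proportions are not an objection to the sample size. This stands as far as it goes, but the abstract and Discussion contradict it, so the protocol does not settle the matter.

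Three stronger readings are tempting, and the document does not support them:
- A reader might infer that the protocol claims 80% power for response and remission. It never says so. Its conclusion is loosely worded, but the preceding sentence ties it to depression severity.
- A reader might infer that 48 is miscalculated because of the binary outcomes. It is not: it reproduces as a one-tailed t-test. The defect is that the calculation and the list of primary outcomes do not match.
- A reader might set the stated 80% against 30% to 56% and blame the whole gap on dichotomising. Part of it is the number of tails; compared two-tailed throughout, the means comparison has 71%.

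It is also fair to object that the protocol gives no sham rates, so any power for proportions is conditional. The ranges move with the sham rate, the latent distribution and the number analysed. The conclusion that two-tailed power is below 80% held in every scenario tried.

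**Conclusion.** The concern holds in a conditional form and should be corrected. The power statement belongs to a comparison of means and reaches 80% at 24 per arm only one-tailed, against the protocol's own two-tailed rule. The sections disagree on whether response and remission are primary. If they are, the stated power does not cover them: on the assumptions above, two-tailed power lies between 23% and 60%, depending on the test, the sham rate and how drop-outs are handled, and is at most about 70% under the more favourable logistic conversion. If they are not primary, the power point falls away, and what remains is the contradiction over their status and the one-tailed basis of the 80%.

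**What to change.** Keep the planned N of 58.

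1. Reconcile the abstract, the Primary outcome section and the Discussion so that the HDRS-17 change is the single primary outcome. Make response and remission supportive, reported as risk differences with 95% CIs, and do not read non-significance as absence of effect.
2. In Sample size calculation, limit the power statement to the HDRS-17 change and state the number of tails. For a two-tailed t-test, power is 71% at 24 per arm and 79% at 29.
3. If power for response or remission is quoted, give it as conditional on the assumed sham rates and the number analysed, without attaching the 24-per-arm range to the 29 recruited. Alternatively, give the detectable difference: about 34 to 43 percentage points at 24 per arm, or about 31 to 40 at 29 per arm with no losses.

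This needs no extra patients, visits or data. The cost is a less favourable stated power and a formal amendment: the section on communicating protocol amendments treats changes to outcomes and analyses as significant, requiring ethics approval, written notice to those concerned and a registry update.

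### The 48 evaluable patients match a one-tailed t-test, but the planned tests are two-tailed: on the protocol's own sizing basis power is about 0.71, not 0.80

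*Protocol article*

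**What the plan says.** The Sample size calculation section of the protocol article names its software ("The sample size will be determined using G*Power 3.1") and takes its effect size, Hedges' g = 0.743, from a meta-analysis of tDCS in adults with MDD. With 80% power and a 5% alpha it concludes that "a total sample size of 48 patients (24 in each group) is required to detect significant differences between the groups". It then adds: "To account for a 20% drop-out rate, a total of 58 patients (29 in each arm) will be recruited". The section gives no number of tails, no test family, and no correlation or covariate.

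The Statistical analysis section says: "The hypotheses will be tested using unpaired, two-tailed tests at a significance level of 0.05". On the analysis set it says: "The primary outcome will be analyzed based on the intention-to-treat principle, with worst case imputation applied". It names the Mann–Whitney U test for between-group comparisons of continuous variables and a mixed linear model for repeated continuous outcomes.

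**The concern.** The sample size and the planned test should share the same alpha and the same sidedness. Here the stated inputs do not lead to 48 patients under the two-tailed test that the analysis section fixes, and the gap of 12 evaluable patients is too large to be rounding. The allowance for dropout also looks short on the section's own terms, because 58 less 20% is fewer than the 48 said to be required.

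The power claim is at stake. The Introduction justifies this trial, after a pilot of 39 adults, by the need for an adequate sample size to confirm efficacy. If the stated 80% is too high, a null result would be read as coming from a better powered trial than it was. Type I error is not affected, since the planned tests are already two-tailed.

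**Working it through.** **Inputs.** From Sample size calculation: d = 0.743, power 0.80, alpha 0.05, 24 per arm evaluable, 20% dropout, 29 per arm recruited. From Randomization, concealment, and blinding: 1:1 allocation. From Statistical analysis: two-tailed tests at 0.05.

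**Formula.** For a two-sample t-test with n per arm, df = 2n − 2 and the noncentrality is d × √(n/2). One-tailed power is P(T > t at 0.95), where T is noncentral t. Two-tailed power is P(|T| > t at 0.975).

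**Step 1: reproduce the stated 48.** At n = 24 the noncentrality is 0.743 × √12 = 2.574 with df = 46.

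| n per arm | One-tailed power | Two-tailed power |
|---|---|---|
| 23 | 0.798 | 0.693 |
| 24 | 0.813 | 0.712 |
| 29 | 0.875 | 0.794 |
| 30 | 0.885 | 0.808 |

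One-tailed, 23 per arm falls just short of 80% and 24 is the smallest number that reaches it. This is exactly the stated figure.

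**Step 2: apply the planned test.** Two-tailed, the smallest n that reaches 80% is 30 per arm, or 60 evaluable. The normal approximation gives 29 per arm (58 evaluable), so the choice of approximation does not explain 48. With 48 evaluable, two-tailed power is 0.712.

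**Step 3: dropout.** 48 × 1.2 = 57.6, rounded up to 58. The number that leaves 48 after a 20% loss is 48 / 0.8 = 60. Conversely, 58 × 0.8 = 46.4, about 23 per arm, with two-tailed power 0.693. The most dropout that 58 can absorb while keeping 48 is 1 − 48/58 = 17.2%.

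**Step 4: detectable effect.** Solving the two-tailed formula for 80% power gives d = 0.826 at 24 per arm and d = 0.845 at 23 per arm.

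**Step 5: all 58 analysed.** With 29 per arm and the effect unchanged at 0.743, two-tailed power is 0.794. The documents do not say how far worst case imputation would dilute the effect. As an assumed range, 10% dilution (d = 0.669) gives 0.71 and 20% dilution (d = 0.594) gives 0.60.

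**The case against.** The strongest reply is that the completer t-test is not the planned analysis. The plan is intention-to-treat, so all 58 may be analysed, and with an undiluted effect two-tailed power is then 0.794, almost the stated 80%. This stands as a limit on the size of the point. It does not remove it, for two reasons. The sample size section itself counts only the 48 patients left after dropout. And worst case imputation for dropouts may dilute the effect, so 0.794 is not assured.

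A second reply is that a mixed model or a baseline-adjusted analysis would be more efficient. By the normal approximation, a baseline correlation of about 0.4 would bring the two-tailed requirement to 24 per arm if g is in endpoint SDs. But the section states no correlation or adjustment, so the printed 48 cannot be shown to rest on one. The Mann–Whitney test works slightly the other way: with efficiency 0.955 under normality, two-tailed power is about 0.69 at 24 per arm and 0.67 at 23.

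Two stronger readings are tempting. A reader might infer that the authors did run a one-tailed calculation. The section does not say so; this is only the two-sample t-test setting that returns 24 from the stated inputs. A reader might also take 0.69 to 0.71 as the trial's true power. The documents do not support that, because the actual power depends on the imputation, the model and the correlations, none of which enter the sizing.

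It is also fair to say that the dropout slip is minor. It is two patients, and it moves two-tailed power only from 0.712 to 0.693. Nearly all of the shortfall comes from sidedness.

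**Conclusion.** The point holds. As printed, the sample size section and the analysis section do not agree: g = 0.743, 80% power and a two-tailed 5% test need 60 evaluable patients, not 48. On the basis that the protocol itself uses, taken as an unadjusted two-sample t-test on evaluable patients, two-tailed power is 0.71 with 48. It is 0.69 with the 46 that remain of 58 after 20% dropout. On that basis a true effect of 0.743 would be missed about 3 times in 10, where the protocol implies 2 in 10.

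The conclusion that 48 does not give 80% two-tailed power on this basis does not depend on how 48 was obtained. The consequence is an overstated power claim, not an invalid analysis.

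**What to change.** Keep 58 randomised and correct the paragraph. Suggested wording: *With 58 randomised and 20% dropout (46 evaluable), a two-tailed 5% two-sample t-test has about 69% power for a standardised difference of 0.743; 80% power is reached at about 0.85.* State the number of tails and the test used. Correct the dropout sentence to say that 58 preserves 48 evaluable patients with up to 17% dropout.

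If the authors wish to mention the gain from baseline adjustment, it should be labelled as an assumption, because the protocol gives neither the correlation nor the SD in which g is expressed. At 23 per arm, for baseline correlations from 0.3 to 0.6, two-tailed power falls from 0.86 to 0.79 if g is in change-score SDs, and rises from 0.73 to 0.87 if g is in endpoint SDs.

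The cost is one reworded paragraph and a less favourable stated power. No extra patients are needed. For comparison, holding to 80% two-tailed power on the present basis with 20% dropout would take 60 / 0.8 = 75 randomised, or 76 at 1:1.
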